### Qualitative data collection

Various qualitative data sources and methods will be used to study the co-construction mechanisms of the implementation of the PA program (obj 1), identify the enabling and inhibiting factors influencing PA integration (obj 2), assess the effects of the intervention (obj 3), and identify ethical and legal issues (obj 4). The triangulation of the data sources will contribute to the internal validity of the study [42].

#### Field documents

A document review will be conducted to study the evolution of the integration of the PAs in the health and social care oncology teams. It will include meeting minutes, action plans, emails, and other relevant documents produced during the project.

#### Interviews

At the beginning and the end of the study, semi-structured interviews will be conducted with approximately five stakeholders from each of the six settings among the directorates, the managers, the administrators/clinicians who will participate in the implementation of the PAs (total *n* = 60 (5x2x6)). As per qualitative research methodology, data collection and analysis will be concurrent, thus the actual number of interviews completed will be determined by data saturation, defined as no more new data/themes emerging from the interviews [43]. The interviews will focus on participants’ expectations of and experience with the implementation of the PA program, the facilitating and hindering factors, their perceptions of the stakes, and how to sustain the intervention. The interview guide will be developed and co-constructed with patients specifically for this study and will be pilot tested with a few people from the target population (see Additional file 1). Interviews will take place in the health care organization concerned or over the phone depending on the participant’s preference and be conducted by the research assistant. They will briefly describe their role in the project and their experiences with qualitative research to the participants. With the consent of the participants, an audio recording of the interview will be made, and field notes will be taken during the interview. They are scheduled to last 60 min.

#### Focus groups

In each setting, at the beginning and end of the project, two focus groups of eight to 12 participants among the representatives of the health and social care team, administrators, patients and PAs participating in the implementation of the PA program [44], will be conducted (total *n* = 12 (2 × 6)). The focus groups will address participants’ perceptions of their experience with the PAs, the interactions between the patients and the PAs and professionals, and the perceived effects of the program on the patients, the PAs and the health and social care oncology team. The focus group guide will be developed and co-constructed with patients specifically for this study and will be pilot tested with a few people from the target population (see Additional file 2). Focus groups will take place in the health care organization concerned and be conducted by the research assistant. They will briefly describe their role in the project and their experiences with qualitative research to the participants. With the consent of the participants, an audio and video recording of the focus group will be made, and field notes will be taken during the focus group. They are scheduled to last 90 min. However, the duration of the focus groups could be extended beyond the planned duration if new data/themes emerge in relation to the questions until saturation is reached.

#### Research logbook

A logbook will be used by the research assistant at each site to collect data regarding the context (the PA program chosen), the mechanisms of co-construction of the PA program (obj 1), the factors that facilitate and hinder the implementation (obj 2), the interactions among health and social care team (obj 3), PA and patients (knowledge exchange, tool used, evolution over time) (obj 3), the perceived influence of these dynamics on patients’ experience of care and quality of life (obj 3) and on the PAs and other health and social care team members experience of the PA program (obj 3), and the ethical and legal issues faced (PA status, PA training, PA integration into the clinical team, etc.) (obj 4).

### Qualitative data analyses

Conventional case study methods will be used to analyze the qualitative data [38]: the interviews and focus groups will be recorded and transcribed in full. Content analysis will be used to analyze these data, as well as the documents collected during the study [40] and will be structured in four phases: 1) creating a common codebook through independent near-data coding done by two researchers and discussion around inter-rater differences and using verbatim (about 10% of the verbatim); 2) coding the complete data corpus by one researcher using the codebook to systematize the description of each case; 3) identification of emerging common themes across cases to enrich the conceptual framework; 4) progressive construction of the cases through discussions with each site team. The analysis will be done with the help of the QDA Miner software (version 5.0) [45]. Validity will be ensured by triangulating data sources and this peer review publication of the protocol, peer debriefing during the analysis and case construction, confirmability will be enhanced by triangulation of the multiple data sources [46] and all data will be analyzed through our conceptual framework to help ensure the validity and the plausibility of findings. The COREQ checklist was used to report the methodology of the qualitative part (see Additional file 3).

### Quantitative data collection

Quantitative data collected will help to achieve the second and third objectives. Validated questionnaires will be used to collect data from each stakeholder group. A summary of the data collection timing and frequency is presented in Table 1. The secure online platform REDCAP (Research Electronic Data Capture), an application for building and managing online surveys and databases, will be used to administer the questionnaires, organize the data collection and analyze the data [52].

**Table 1 Tab1:** List and description of quantitative data collection questionnaires

Outcomes	Questionnaires	Dimensions	Number of items	Response scale	Time of measurements	Question numbers in appendices
**Patient reported experience**	Patient’s care experience questionnaire ^a^	• Site of diagnosed cancer; cancer stage at time of diagnosis; type of treatment; date of start of treatments • Consultation in oncogenetics, genetic status, time of disclosure of results of genetic testing, surgery to reduce the risk of developing cancer, time of preventive surgery • Evaluation of information communicated by medical team, support of friends and family.	25 items	Varied	T0	Additional file 4: T0: 41 to 67
	Sociodemographic questionnaire ^a^	• Gender, age, country of origin, region, number of people in the household, number of dependents, family composition, level of education, perception of financial situation.	18 items	Varied	T0	Additional file 4: T0: 22 to 39
	Patient’s experience with PAs questionnaire ^a^	• Topics discussed, benefits and perceived contribution of PA • Expectations of patients that did not benefit from PA accompaniment	14 items	Varied	T0, T1, T2	Additional file 4: T0: 69 to 100 T1: same as T0 T2: 102 to 127
	Treatment adherence questionnaire [47]	• Intention of receiving treatments • Obstacles to treatment	8 items	5 point Likert scale (1 = strongly disagree and 5 = strongly agree)	T0, T1, T2	Additional file 4: T0: 148 to 159 T1: same as T0 T2: same as T0
	CASE [48]	**Ability to cope with cancer** • Understand and participate in care • Maintain positive attitude • Seek and obtain information	12 items	4 point Likert scale (1 = strongly disagree and 4 = strongly agree)	T0, T1, T2	Additional file 4: T0: 129 to 140 T1: same as T0 T2: same as T0
	Kessler Psychological Distress Scale (K6) [49]	• on emotional states	6 items	5 point Likert scale (1 = Always and 5 = never)	T0, T1, T2	Additional file 4: T0: 141 to 146 T1: same as T0 T2: same as T0
**PA reported experience**	PAs’ care experience questionnaire ^a^	• Site of diagnosed cancer; time of diagnostic; type of treatment; date of start of treatments • Consultation in oncogenetics, genetic status, time of disclosure of results of genetic testing, surgery to reduce the risk of developing cancer, time of preventive surgery • Evaluation of information communicated by medical team, support of friends and family.	25 items	Varied	T0	Additional file 5: T0: 39 to 60
	Sociodemographic questionnairev	• Gender, age, country of origin, region, number of people in the household, number of dependents, household situation, level of education, perception of financial situation.	18 items	Varied	T0	Additional file 5: T0: 19 to 36
	Previous personal experience with PAs questionnaire^a^	• Presence of pairing or not with a PA • Topics discussed, benefits and perceived contribution of PA • Expectations of patients that did not benefit from PA accompaniment are also evaluated	14 items	Varied	T0	Additional file 5: T0: 62 to 82
	Kessler Psychological Distress Scale (K6) [49]	• Psychological distress	6 items	5 point Likert scale (1 = Always and 5 = never)	T0, T2	Additional file 5: T0: 84 to 89 T2: idem to T0
	Review of PA experience with patient questionnaire^a^	• Support of clinical team • Quality of tools used • Useful information to effectively carry out their role as PA • Communication with the clinical team • Role in the clinical team • Perceived impact of their intervention on the patient and on the PA themself.	140 items	Varied	T2	Additional file 5: T2: 91 to 241
**Descriptive data of each meeting**	Logbook^a^	• PA name • Patient name • Date, time, duration • Context of the request • People present during the meeting • Context of the meeting • Step of patient trajectory • Topics discussed • Difficulties and questions • Feedback from the clinical team	28 items	Varied	After each meeting	Additional file 6: 3 to 42
**Health professional reported experience**	Adaptation of the Collaborative Practice Assessment Tool (CPAT) [50]	• Perceptions of concepts of collaborative practices, mission and goals of the teams (4 domains out of 8 domains retained and one created for the project) • General Relationships • Team leadership • General role responsibilities, autonomy • Communication and information exchange • Practice evaluation^a^	26 items retained out of 56	7 point Likert scale (1 = strongly disagree and 7 = strongly agree)	T0, T2	Additional file 7: T0: 22 to 47 T2: 103 to 128
	Group Innovation Inventory [51]	• Innovative culture (adaptation)	7 items retained out of 36	7 point Likert scale (1 = strongly disagree and 7 = strongly agree)	T0, T2	Additional file 7: T0: 48 to 54 T2: 129 to 135
	Readiness To Partner With Patient and Family Advisers - Patient and FamilyEngagement in the Surgical Environment Module. Content last reviewed May 2017. Agency for Healthcare Research and Quality,Rockville, MD. https://www.ahrq.gov/hai/tools/ambulatory-surgery/sections/implementation/training-tools/readiness.htm [50]	• Perception of health professionals concerning the partnership with patients (treatment plan, decision making) • Perception of health professionals concerning the role of PAs	11 items retained out of 18	5 point Likert scale (1 = strongly disagree and 5 = strongly agree)	T0, T2	Additional file 7: T0: 64 to 74 T2:145 to 155
	Questionnaire on perception towards the integration of PA in their team^a^	• Perception of the possibility of integrating PAs into the care team and eventual obstacles	5 items	Varied	T0, T2	Additional file 7: T0: 56 to 62 et 75 T2: 137 to 143 et 156
	Readiness To Partner With Patient and Family Advisers - Patient and Family Engagement in the Surgical Environment Module.Content last reviewed May 2017. Agency for Healthcare Research and Quality, Rockville, MD. https://www.ahrq.gov/hai/tools/ambulatorysurgery/sections/implementation/training-tools/readiness.html^a^			Varied	T0	Additional file 7: T0: 80 to 97

^a^ Questionnaire developed for this study by the research team

#### Questionnaires for patients

Measurements will be taken before the meeting with the PA (T0), immediately following this meeting (T1), and again 1 month after this meeting (T2). Two of the questionnaires used will be co-constructed with patients specifically for this study and assess: patients’ care experience (Additional file 4, questions 41 to 67) and patients’ experience with PAs (Additional file 4: questions 69 to 100 and 102 to 127), following the procedures and sequence of content validation outlined by Haynes and colleagues (1995) [53]. Three validated questionnaires will be used to assess patients’ psychological distress (K6) [49] (Additional file 4: questions 141 to 146), treatment adherence [47] (Additional file 4: questions 148 to 159), and ability to cope with cancer (CASE) [48] (Additional file 4: questions 129 to 140). Data variables of patients’ sociodemographic and clinical characteristics will be collected including sex, age, and type of cancer (Additional file 4, questions 22 to 39). To obtain a complete data set for 30 to 50 patients per site and based on a previously established response rate of 70% [54, 55], we will plan to recruit at least 40 to 70 patients from each site.

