## Methods/design

### Study design

The planned approach is a longitudinal multiple in-depth case study with two levels of analysis (clinical and organizational) that will be conducted over 4 years at six different sites. The longitudinal design is necessary to account for inevitable delays over the course of the implementation, to allow the time to consolidate changes made at each case site, and to allow the time needed to avoid making premature conclusions regarding the impacts of the changes [38, 39]. The multiple case study design allows for the in-depth analysis of the implementation processes in diverse oncology contexts. Qualitative and quantitative data will be used to document the intervention for each case, to examine the implementation processes, in their respective contexts, and to report their respective effects at the clinical and organizational levels [40]. This design is consistent with realistic evaluation [30] and intervention action-research [29] and structures our in-depth investigation of the links between the implementation and co-construction mechanisms and our ability to capture the challenges and the effects of the intervention.

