### Governance

Each site will assemble a local project committee made up of PAs, oncologists, administrators, nurses, oncology nurse coordinators, allied health professionals (e.g., social worker or psychologist), and a research assistant. An overarching study committee comprising the research coordinator for all sites, the research assistants of each site, and an administrator/clinician representative from each site will be in charge of setting up the PA program, discussing challenges and finding solutions, and facilitating the assessment. A community of practice of approximately 30 PAs (between 3 to 5 PAs will be recruited per site) will be formed so the PAs can share successes and challenges and learn from one another. Finally, a steering committee made up of the decision makers and researchers will meet annually to discuss the progress of the project, provide advice on how to carry out the research and comment on the results, and an advisory committee made up of the site representatives (the research assistant and the administrator or clinician) and researchers will review and interpret results of each phase of the study.

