#### Health and social care provider questionnaires

To better identify the organizational factors that can influence the integration of PAs in clinical oncology teams, we will administer validated questionnaires to health and social care provider participants at the beginning and end of the study to assess the evolution of their collaborative practices [50] (Additional file 7: questions 22 to 47), their capacity to make changes to their collaborative practice [51, 56, 57] (Additional file 7: questions 48 to 54), their perception about their relations with the patients and the PA’s [50] (Additional file 7: questions 64 to 74) and with a questionnaire that will be developed for this study about their openness to integrating PAs in their team and potential barriers to this integration (Additional file 7: questions 56 to 62 and 75). Sociodemographic data will be collected also **(**Additional file 7: questions 80 to 97)**.** Considering a minimum response rate of 35%, to obtain a sample size of 15 health and social care providers from each site, 43 will be invited, from each setting (*n* = 258 (6X43)), to respond to the questionnaires.

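### At a 70% response rate, the recruitment floor of 40 to 70 patients per site gives about 28 to 49 complete data sets, just short of the 30 to 50 intended (minor)

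*Protocol article*

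**What the plan says.** The patient numbers are in the protocol article under Questionnaires for patients. The aim is stated first, "To obtain a complete data set for 30 to 50 patients per site", followed by an assumed response rate of 70% taken from two cited sources. The conclusion drawn is "we will plan to recruit at least 40 to 70 patients from each site". This is the only sample-size statement for patients in the article.

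The article makes one other calculation of the same kind, under Health and social care provider questionnaires. It begins "Considering a minimum response rate of 35%, to obtain a sample size of 15 health and social care providers from each site" and arrives at 43 invitations per site, or 258 over six sites.

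For patient advisors, the Governance section describes "A community of practice of approximately 30 PAs (between 3 to 5 PAs will be recruited per site". The Study design section describes a study "that will be conducted over 4 years at six different sites".

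**The concern.** The patient sentence links a target, a rate and a recruitment number, so a reader can check whether the third follows from the first two. It does not quite. The recruitment numbers are a little too low at both ends of the range, so a site that recruits exactly to the stated floor should expect to miss the stated aim. The provider calculation shows that the article's own practice is to divide by the rate and round up, and the patient figure departs from that.

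Little is at stake. The target is set per site and the study is built as six case studies, so a site planning its recruitment would work from these numbers. The PA total raises a similar matter: the article gives a per-site range and a number of sites, and the total it quotes is the top of what they allow.

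**Working it through.** **Inputs, all from the protocol article**

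- Complete patient data sets wanted per site: 30 to 50 (Questionnaires for patients)
- Assumed patient response rate: 70% (same section)
- Patients to recruit per site: at least 40 to 70 (same section)
- Provider target and rate: 15 per site at 35%, with 43 invited (Health and social care provider questionnaires)
- PAs per site: 3 to 5, about 30 in total (Governance)
- Sites: 6 (Study design)

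**Provider figure, to establish the article's own method**

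Number to approach = target ÷ response rate, rounded up.

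- 15 / 0.35 = 42.86, rounded up to 43
- 6 × 43 = 258

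Both stated provider figures are reproduced exactly.

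**Patient figure by the same method**

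- Low end: 30 / 0.70 = 42.86, rounded up to 43. The article states 40, which is 3 fewer.
- High end: 50 / 0.70 = 71.43, rounded up to 72. The article states 70, which is 2 fewer.

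The stated 40 to 70 is therefore not reproduced. A common shortcut, adding 30% to the target instead of dividing by 0.70, gives 30 × 1.30 = 39 and 50 × 1.30 = 65. That comes near the lower figure but not the upper, so it does not explain the range. Rounding 42.86 and 71.43 to the nearest ten gives 40 and 70, which is the likeliest origin.

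**Expected yield at the stated floor**

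- 40 × 0.70 = 28, against 30 wanted: 2 short
- 70 × 0.70 = 49, against 50 wanted: 1 short

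Put the other way, 40 recruits give 30 complete data sets only if the rate is 30/40 = 75%, and 70 recruits give 50 only if it is 50/70 = 71.4%.

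**Cost of meeting the target**

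Over six sites the floor would rise from 6 × 40 = 240 to 6 × 43 = 258 at the low end, and from 6 × 70 = 420 to 6 × 72 = 432 at the high end. That is 18 or 12 more patients in all. These totals are multiplied out here; the article gives no overall patient number.

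**PA total**

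- 6 × 3 = 18
- 6 × 5 = 30
- Midpoint: 6 × 4 = 24

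A total of 30 is reached only if every site recruits its maximum of 5.

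**The case against.** The strongest answer is that this is rounding and nothing more. The article says at least 40 to 70, which is a floor, and under Participants it says that everyone who meets the criteria will be invited, by consecutive sampling. Nothing stops a site from recruiting 43 or 72. The gap of 1 or 2 complete data sets is also small beside a target that is itself 20 patients wide. The study is an in-depth feasibility case study with no stated power calculation, so no analysis or decision rule changes.

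Most of that stands, and it is why the point is minor. What remains is that a floor is offered as enough to reach the aim, and at both ends it falls slightly short. The article also rounds the same 42.86 up to 43 in the provider calculation, so rounding down is not its general practice.

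On PAs, the answer is that 30 lies inside the possible range and that the sentence describes the size of a community of practice, not a sample size. That is fair. The wording is loose but not contradictory.

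A reader might infer something stronger about patients. Data are collected before the meeting, immediately after it and one month later, so the 70% might seem to need applying at each wave, with a much lower yield. The article does not support that. It attaches the 70% directly to obtaining a complete data set, and the natural reading is the share of recruited patients with complete data. A per-wave loss would also need an assumption about independent dropout that the article nowhere makes.

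**Conclusion.** The point holds as a minor arithmetic correction. Taking the 70% as the proportion of recruited patients who provide a complete data set, and recruitment at exactly the stated floor, the expected yield is 28 to 49 per site, not 30 to 50. The minimum needed for 30 to 50 is 43 to 72. The shortfall is 2 and 1 patients per site.

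It would go too far to conclude that the study is under-sized or that its patient analyses are compromised. The article states no power or precision target for these numbers to fail, and the recruitment figure is open upwards. It would also be wrong to say that the article states an overall patient total that is missed, because it states none.

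The PA total is a smaller matter of the same kind: 18 to 30 is what the per-site range allows, and the article quotes the maximum as though it were the expected figure.

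**What to change.** Make one of two changes under Questionnaires for patients:

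- keep the recruitment floor of 40 to 70 and restate the expected yield as about 28 to 49 complete data sets per site; or
- keep the aim of 30 to 50 and state the recruitment floor as 43 to 72 per site.

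The first costs only wording. The second adds 3 recruits per site at the low end and 2 at the high end.

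Under Governance, give the PA total as 18 to 30, or as up to 30. This is wording only.

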#### Questionnaires for patient advisors

For the PAs, outcome measurements will include one validated questionnaire to evaluate psychological distress (K6) [49] (Additional file 5: questions 84 to 89), and 3 questionnaires will be developed for this study: PA’s care experience (Additional file 5: questions 39 to 60), previous personal experience with PAs (Additional file 5: questions 62 to 82), and a descriptive review of their PA experience with patients during the project (Additional file 5: questions 91 to 241**).** Sociodemographic data will be collected also **(**Additional file 5: questions 19 to 36)**.**

